### Modifying the interventions and adherence to protocol

The INSTRUCT protocol is the same in all communities across the five intervention districts, but the details of how the intervention plays out will differ between communities and between districts, with local stakeholders determining exactly what they do and how they do it. This participatory approach to RCTs of interventions for public health issues is gaining momentum [46–49], as it allows contextualisation of and local buy-in to a standard intervention. A trial of community mobilisation for prevention of dengue in Mexico and Nicaragua that took this approach demonstrated a significant impact on entomological indices and on rates of serological dengue infection and clinical dengue illness [50–52].

In addition to following up young women after workshops, the district coordinators and INSTRUCT investigators will maintain frequent contact with government program officers and managers and with trained BVV facilitators. We expect a considerable turnover of trained community facilitators, health education assistants and teachers so that further trainings of audio-drama facilitators will be necessary. We will use social network analysis to examine the networks of young women for information, socialising and emotional support, and the way such networks might be used to reach young women with information – for example about government support programs – more effectively.

Recognizing that local context can affect the impact differently from district to district, we will carry out mid-stream intervention research that will map out these context factors using a mixture of written and oral narratives, key informant interviews, impact logs, and inter-organizational network analysis [53]. We will use the Most Significant Change technique to explore change dynamics and language [54]. The concern of this intervention research within INSTRUCT is how intervention effects are modified by context.

### Outcomes

The *primary outcome* is HIV prevalence in young women aged 15–29 years, measured in an impact survey in the five intervention and five control (second wave of intervention) districts. We will undertake rapid HIV screening testing, using Alere Determine units to test finger prick blood samples for HIV1 and HIV2 antibodies. We will not perform confirmatory testing for those that test reactive on this screening test. However, those reactive on the screening test will be referred to their local government clinic for confirmatory testing, counselling, and treatment if appropriate.

*Secondary outcomes* will rely on responses to a questionnaire for men and women aged 15–29 years administered in the impact survey in intervention and control districts. We will measure intermediate outcomes between knowledge and behaviour, according to the CASCADA behaviour change model [55, 56], based on the Theory of Planned Behaviour [57]. CASCADA is an acronym for a partial order of intermediates between knowledge and action: Conscious knowledge, Attitudes, Subjective norms, intention to Change, Agency to make the change, Discussion with family, peers and neighbours, and finally Action. The model does not assume that intermediate steps between conscious knowledge and action are necessarily linearly related. We have used the CASCADA model in resource-poor settings to support analysis and interpretation in cross-sectional studies examining health-related behaviours [58, 59], to guide design of interventions [50, 60, 61] and as a framework for qualitative and quantitative analysis of intervention effects [62, 63]. In this trial, the questionnaire will collect information on the CASCADA sequence of intermediate variables for use of government programs, engagement in transactional sex, gender violence, physical intimate partner violence, multiple partners, and condom use.

We will document costs of the intervention to estimate the cost per HIV case avoided. Monthly budgets and review of actual expenditure, for central and district activities, will provide the basis for documenting costs. In parallel, records of grants and loans made to marginalized young women by government structural support programmes will document this additional expenditure focused on HIV prevention. Estimated intervention costs will include pro-rated salary costs of government personnel who spend part of their time implementing the interventions (such as health education assistants and teachers facilitating BVV sessions). Salary and other costs of the central team activities will form a separate category as only a proportion of these costs will be incurred by the programme if it is successfully rolled-out more widely and longer-term.

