These government structural support programs were not designed to benefit young women or to prevent HIV. Use by marginalised young women is low: in a recent study among young women aged 18–29 years who were not in school and not in work, only 33% of young women had ever applied and 10% had ever benefitted from any program, excluding a part-time minimum wage rotating employment scheme with no training or development elements. More educated young women were more likely to be accepted into these programs, indicating a double disadvantage for those who had dropped out of school, for example due to unplanned pregnancies [24].

The Inter-ministerial National Structural Intervention trial (INSTRUCT) arose from discussions in the Botswana HIV Prevention Think Tank, a high-level government advisory body convened by the National AIDS Coordinating Agency (NACA). Recognising the dearth of robust evidence of the impact of structural interventions for HIV prevention, NACA and CIET proposed a national cluster randomised controlled trial of a structural intervention.

The research question is: Can a structural intervention, applied at district level to increase the access of marginalized young women to government structural support programs and provide an enabling environment for their emancipation, reduce HIV infections among these young women?

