### Specific objectives

Implement, in five randomly selected districts, a composite structural intervention: to build skills and support young women to apply to available government support programs; to make support programs more accessible to young women; and to create an enabling environment for young women to exercise protective choices.Measure the impact of the intervention on HIV rates in marginalized young women aged 15–29 years living in intervention districts, compared with young women living in five randomly selected control districts.Measure the impact of the intervention on intermediate outcomes in a behaviour change model in young women and young men, comparing intervention and control districts.Document costs of the intervention package in relation to its outcomes, to calculate costs per case averted and confront the cost implications of its wider roll-out.

A broader outcome, if the trial indicates impact on HIV rates, will be to stimulate further trials of structural interventions appropriate to the context with HIV infections as an endpoint. This will be relevant in Southern Africa and in other regions. In the meantime, the findings from Botswana should make a case for scaling up the interventions in that country.

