## Methods

### Study setting

Botswana, in Southern Africa, is roughly the size of France, with a population of about two million, mainly concentrated in the South East around the capital, Gaborone. The adult (15–49 years) HIV prevalence in Botswana at 21.9% in 2016 is amongst the highest in the world [38]. Women are disproportionately affected, with an adult prevalence of 26.3%, compared with 17.6% among men [38]. Despite prevention efforts, the incidence of new HIV infections in Botswana has been resistant: the 2013 Botswana AIDS Impact Survey (BAIS IV) reported an (uncorrected) HIV annual incidence of 2.92% in the population aged 18 months to 64 years, the same as the equivalent figure in the 2008 BAIS III survey [39]. The BAIS IV “raw” incidence figures for both 2008 and 2013 are over-estimates of incidence but they illustrate the lack of important reduction in incidence. The 2016 UNAIDS estimate for HIV incidence in adults aged 15–49 in Botswana is 9.32 per 1000 [38].

The Botswana government provides a range of programs offering grants or loans, intended to help people improve their educational qualifications, start small enterprises, build skills to increase employability, and improve livelihoods. Young women and men of 18 years and above are eligible for most of these programs, and some specifically target youth. Up to eight ministries are involved in planning and managing these programs. Programs include support for growing crops or keeping livestock, support to return to school or use distance learning, a youth apprenticeship scheme, a scheme to support youth enterprises, various schemes for those below a poverty line, training and support for entrepreneurship, and a rotating minimum wage part-time employment scheme, *Ipelegeng*, which does not provide any training or development support for participants, but is easy to apply for and readily available, especially in more remote areas.

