#### Focused workshops (FW) for young women

This intervention combines advice and training for young women with helping them to take advantage of existing government support programs. It aims to increase self-esteem and assertiveness, as well as provide access to income-generating support programs, so transforming HIV risk. District INSTRUCT field coordinators in each intervention district, trained by the central team of INSTRUCT investigators, will implement FW in each community in the district. The District coordinators will try to identify all young women aged 15–29 in each community who are not in school and not in work. We have developed a method – respondent-driven recruitment – to do this, derived from respondent-driven sampling. Local field workers will identify and interview eligible young women by going door to door, by asking eligible young women to direct them to other eligible young women, and by seeking the advice of community leaders, social workers and health education assistants in each community. Our field workers will be young women from the district, and their knowledge will be important in identifying eligible participants.

They will interview these young women and invite those aged 18–25 years to attend a two-day workshop. Each workshop will have about 20–25 participants, and the number of workshops required in each community will vary. The interactive workshop will cover skills of communication, negotiation, resisting peer pressure, and building assertiveness and self-esteem. On the second day of the workshop, local program officers from government support programs will attend to talk about their programs and answer questions about how to apply. The workshop intervention will not itself provide capital or loans; these will come from the existing programs. The district coordinators will follow up young women participants after the workshops to check their progress and help to resolve difficulties with access to programs.

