#### Statistical methods

We will adopt an intention-to-treat principle for measuring primary outcomes with district as the unit of analysis. The primary analysis will treat the two groups of districts as a parallel design, and will use a two-sample t-test to compare the HIV prevalence rate of young women aged 15–29 years in the five first wave (intervention) and the five second wave (control) districts. Since the impact assessment in the first wave will coincide with the baseline in the second wave, the analysis will be able to ignore temporal effects.

Secondary analysis will compare HIV and gender violence related knowledge, attitudes and behaviours in young women and men between intervention and non-intervention districts, adjusting for clustering. Adjusted analysis using regression techniques will investigate the residual impact of key baseline characteristics on the outcomes. We will examine the residuals for model assumptions and chi-squared test of goodness-of-fit. Analysis will rely on CIETmap software [70] which provides a windows interface with the statistical programming language R.

We will summarize district demographics and outcome variables (both primary and secondary) using descriptive measures: mean (standard deviation) or range (minimum-maximum) for continuous variables and number (percent) for categorical variables.

Sensitivity analysis will examine correlated outcomes using generalized estimating equations, assuming intervention as a fixed effect, district as clustering variable and an exchangeable or unstructured covariance structure to model correlation of participants within a district. Planned subgroup analysis will focus on subgroups of young women with different exposures [71]. Age is a core issue in gender violence and HIV incidence. A history of sexual abuse is likely to affect responses across a range of themes. Variables on use of alcohol and other substances may be informative, as well as employment or educational status and exposure to workshops in the intervention districts.

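### Recorded grants and loans are labelled additional spending with no deduction for awards that would have been made anyway, and their place in the cost per HIV case avoided is left open

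*Protocol article*

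**What the plan says.** The fourth item under Specific objectives is to "Document costs of the intervention package in relation to its outcomes, to calculate costs per case averted" and to face what wider roll-out would cost. The costing paragraph in Outcomes opens with the same purpose: "We will document costs of the intervention to estimate the cost per HIV case avoided". It takes central and district budgets and actual spending as the basis. It then adds that, alongside these, "records of grants and loans made to marginalized young women by government structural support programmes will document this additional expenditure focused on HIV prevention". The next sentence says that "Estimated intervention costs will include pro-rated salary costs of government personnel who spend part of their time implementing the interventions". Central-team costs are placed in a category of their own.

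Three other places describe the programmes. Study setting says: "The Botswana government provides a range of programs offering grants or loans". The section on focused workshops says: "The workshop intervention will not itself provide capital or loans; these will come from the existing programs". The Background reports that, among women aged 18–29 not in school and not in work, "only 33% of young women had ever applied and 10% had ever benefitted from any program", leaving out one part-time employment scheme.

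The health effect is a contrast between arms. Statistical methods plans a two-sample t-test on districts "to compare the HIV prevalence rate of young women aged 15–29 years in the five first wave (intervention) and the five second wave (control) districts".

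**The concern.** The costing paragraph treats a record of awards as if it were a measure of additional spending. Some marginalised young women obtained programme support before the trial. Nothing in the article suggests that this stops in either arm, so some recorded awards are not due to the intervention.

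The effect side of the ratio already has its counterfactual: cases averted is intervention districts compared with control districts. A cost per case averted needs a cost side built the same way. The article states no such comparison for awards and does not say whether awards belong in the ratio.

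At stake is the figure meant to inform roll-out. An overstated cost per case could count against extending the package, and an understated one could make it look cheaper than it is.

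**Working it through.** **No figure to reproduce.** The article gives no unit cost, number of awards, total cost or cost per case. The check sets the sections side by side and then illustrates how far gross and net awards could differ.

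**Side by side**
- Outcomes: recorded awards are called additional.
- Study setting and the focused-workshops section: the money comes from programmes that already exist.
- Background: 10% of the women surveyed had already benefitted, so awards without the intervention are not zero.
- Statistical methods: the effect is net of control districts.

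Recorded awards therefore consist of a background part and an increment, and only the increment matches the effect.

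**Illustration 1: awards only.** Let b0 be the share benefitting without the intervention and b1 the share with it, with equal mean award (assumption).
- Share of awards not due to the intervention: s = b0/b1.
- Gross awards divided by the increment: b1/(b1 − b0).

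| b0 | b1 (assumed) | s | gross/increment |
|---|---|---|---|
| 10% (Background) | 15% | 67% | 0.15/0.05 = 3.0 |
| 10% | 20% | 50% | 0.20/0.10 = 2.0 |
| 10% | 30% | 33% | 0.30/0.20 = 1.5 |
| 10% | 50% | 20% | 0.50/0.40 = 1.25 |
| 5% (assumed) | 15% | 33% | 0.15/0.10 = 1.50 |
| 5% | 20% | 25% | 0.20/0.15 = 1.33 |
| 5% | 30% | 17% | 0.30/0.25 = 1.20 |
| 5% | 50% | 10% | 0.50/0.45 = 1.11 |

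**Illustration 2: cost per case.** Let g be the share of total cost made up by gross awards. The article does not give it, so it is assumed. Setting that total to 1, the correct total is 1 − g·s.
- Awards entered gross: cost per case is 1/(1 − g·s) times the correct value.
- Awards left out: cost per case is (1 − g)/(1 − g·s) times the correct value.

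| g (assumed) | s | entered gross | left out |
|---|---|---|---|
| 0.2 | 20% | 1/0.96 = 1.04 | 0.8/0.96 = 0.83 |
| 0.2 | 67% | 1/0.867 = 1.15 | 0.8/0.867 = 0.92 |
| 0.5 | 20% | 1/0.90 = 1.11 | 0.5/0.90 = 0.56 |
| 0.5 | 67% | 1/0.667 = 1.50 | 0.5/0.667 = 0.75 |
| 0.8 | 20% | 1/0.84 = 1.19 | 0.2/0.84 = 0.24 |
| 0.8 | 67% | 1/0.467 = 2.14 | 0.2/0.467 = 0.43 |

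**Limits.** The 10% is the share who had ever benefitted, at ages 18–29 and excluding one scheme. It is not a rate of awards over the trial period, so it is only a stand-in for b0. The values of b1 and g, and equal award size, are assumptions. The tables show direction and possible scale and do not estimate this trial's error.

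**The case against.** The strongest reply is that the article fixes no costing formula. Awards are recorded alongside the project budgets, the sentence on estimated intervention costs names salaries and not awards, and the workshops themselves provide no capital. *Additional* may mean only spending beyond the project's own budgets. Rules for counterfactual and valuation often sit in a full protocol or economic plan, which is not shown, and nothing in the article forbids netting. Programme use is also asked about in the impact survey in both arms.

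Much of this stands. A reader might infer that every grant and loan in the intervention districts goes into the numerator at full amount. The text does not say that: it sets no district limit, states no inclusion rule and does not say that all awards count. A reader might also infer that loans are added to grants at face value. The article has no rule on valuation or repayment, so that inference has no support and forms no part of this point.

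Two things remain. First, the paragraph's declared purpose is the cost per case, and it calls the recorded awards additional HIV-prevention spending. That is a statement in the text, and it does not fit the background use that the article itself reports. Second, the ambiguity does not rescue the ratio. Gross inclusion overstates it, and exclusion omits spending the article itself calls additional. The survey item helps with uptake but is not said to collect award amounts.

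**Conclusion.** The point holds in a limited form. Recorded awards are equated with additional expenditure although part of them would have been made anyway, and the article does not say whether or how they enter the cost per HIV case avoided. It would go too far to say that the plan divides a gross cost by a net effect: that is one of two readings, and both need the increment.

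The size cannot be fixed from the documents. With b0 at 10% and assumed uptake of 15–50%, gross awards would be 3.0 to 1.25 times the increment. If gross awards were also half of total cost, the cost per case would be 1.11 to 1.50 times the correct value with awards entered gross, or 0.56 to 0.75 times with awards left out. All of this rests on the assumptions listed in the working.

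Only the cost objective is touched. The HIV comparison, its sample size and the randomised contrast are unaffected.

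**What to change.** In the costing paragraph of Outcomes, state that:
1. additional programme expenditure is awards per eligible young woman in the five intervention districts minus the same quantity in the five control districts, over the same calendar period and from the same programme records;
2. this increment enters the cost per case averted;
3. gross awards are reported separately as budget impact.

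The cost is one paragraph of wording and a request for the same records in the second-wave districts, with no added participants or procedures. The downside is that control-district records may be patchy. Risks and mitigation strategies describes access to the programmes as uneven and says that better monitoring, including beneficiaries' age and sex, is still to be developed, so the request is best made in advance. If the records fall short, the survey item on programme use, collected in both arms (Outcomes; Data collection and analysis for impact measurement), can scale uptake. It cannot supply award amounts, which would then have to be stated as an assumption.

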### Participant timeline

The schedule of district allocation, interventions and impact assessment is shown in Fig 1. Enrolment in the first wave of five districts will begin in mid-2014 and continue to the end of 2018. We will begin the intervention in one of the five districts, extending to the other four in years 2–3 of the project.

**Fig. 1 Fig1:**
[figure not shown]
Schematic representation of the study design and timelines

### Sample size

The intervention package will potentially affect all young women in each intervention district. However, the impact assessment will rely on a cluster random sample of communities drawn from the recent census. There are thus two quite different domains – the domain of intervention (*all* young women in the intervention districts) and the domain of the survey (the *sample* of villages or clusters that will provide evidence of the impact on young women in the district) within which we will include all young women with no sub-sampling within the cluster.

Sample size calculations for the survey used a calculator developed by Taylor and colleagues [64]. The HIV prevalence in Botswana control clusters in the 2012 impact assessment was 23% among women aged 15–29 years ([name], personal communication). In the Botswana AIDS Impact Survey of 2013, the HIV prevalence among women aged 15–49 years was 28.2% [39]. Since districts are the unit of randomization, intervention and analysis, starting from 23% (range 17–28%, k = 0.119), 650 women per district in five districts in each arm would detect a reduction to 17.25% (25% reduction in HIV) at the 5% significance level with 80% power. In the unpublished three-country study, the combined interventions in Botswana produced a reduction in HIV of around 50% ([name], personal communication); these sample size calculations therefore allow for some inefficiency in taking the interventions to scale.

We will select a stratified random sample of 10 clusters (enumeration areas) from each of the five intervention districts, and 10 from the control (next wave of intervention) districts. From each cluster we will interview and test for HIV (rapid screening testing of finger prick blood) around 100 young people aged 15–29 years (at least 65 of them women). The sample will include around 5000 people from intervention districts and 5000 from non-intervention districts. To achieve these numbers, the overall sample size *invited to participate* in the survey will need to be around 7500 to allow for absentees and those who decline to participate. Some 13.1% of young women contacted in the 2012 survey in the three countries declined to participate, and a further 14% were absent at the times the interviewer could visit ([name], personal communication).

Secondary outcomes (such as gender violence, unsafe sexual behaviours) are more common occurrences and the power to detect these is correspondingly greater.

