We will use multiple-imputation to deal with missing data [72]. All statistical tests will be two-sided at the 0.05 level of significance. The Bonferroni method will adjust the level of significance for testing for secondary outcomes to keep the overall level at alpha = 0.05. We will express results as effect or odds ratio/relative risk reduction for binary outcomes, standard errors, corresponding two-sided 95% confidence intervals and associated *p*-values.

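### The 80% power treats 650 women per district as a simple random sample, although they come from 10 sampled enumeration areas; if k = 0.119 is a true between-district figure, a variance component is missing and there is no slack.

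*Protocol article*

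**What the plan says.** The Sample size section sets the calculation at district level: "Since districts are the unit of randomization, intervention and analysis", it proceeds "starting from 23% (range 17–28%, k = 0.119"), and concludes that "650 women per district in five districts in each arm would detect a reduction to 17.25% (25% reduction in HIV"). The operating characteristics claimed for this comparison are stated as "at the 5% significance level with 80% power". The Statistical methods section makes the test two-sided ("All statistical tests will be two-sided at the 0.05 level of significance") and names a two-sample t-test on the prevalences of five intervention and five control districts as the primary analysis.

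The survey has a further sampling stage. "We will select a stratified random sample of 10 clusters (enumeration areas) from each of the five intervention districts", with 10 from the control districts, which the Data collection section makes 10 in each. Each EA supplies "around 100 young people aged 15–29 years (at least 65 of them women"), so 10 × 65 = 650 women per district.

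One k is given. The section does not say whether 17–28% is a range of true district prevalences, of survey estimates, or of the 2012 control clusters from which the 23% comes. It gives no ICC, coefficient of variation or design effect for EAs within a district.

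**The concern.** A district prevalence estimated from 10 sampled EAs carries the variance from having drawn those 10 and not others. Taking all eligible women in a chosen EA does not remove it, because the EAs are themselves a sample. A calculation that uses a between-district k plus simple binomial variance on 650 women leaves this component out.

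The 80% is the yardstick for reading a null result in a ten-district trial meant to inform national roll-out. If the true figure is lower, a null result would be given more weight than the design can bear. The validity of the primary test is not at stake: EA sampling variance enters the observed spread of the district prevalences, so the t-test and its confidence interval already reflect it.

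**Working it through.** **Inputs from the article.** p0 = 0.23, p1 = 0.1725, difference 0.0575; k = 0.119; n = 650 women per district; c = 5 districts per arm; two-sided 5%; 80% power; t-test with 2 × 5 − 2 = 8 df; 10 EAs of 65 women.

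**Assumed input.** The EA-level ICC within a district is not given; a range of 0.002 to 0.03 is shown.

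**1. Reproducing the plan's figure.** The standard unmatched cluster formula is

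c = 1 + (1.96 + 0.84)² × V / (p0 − p1)², with V = [p0(1−p0) + p1(1−p1)]/n + k²(p0² + p1²).

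- Binomial part: (0.1771 + 0.1427)/650 = 0.000492
- Between-district part: 0.119² × (0.0529 + 0.0298) = 0.001170
- V = 0.001663
- c = 1 + 7.849 × 0.001663/0.003306 = 4.95, rounded up to 5

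Power at c = 5 is 80.5% by this formula and 78.8% by the non-central t on 8 df. The stated 80% is therefore reproduced, with the 650 women entering as independent draws and no EA term.

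The value of k agrees with the quoted range divided by four, over the mean: (0.28 − 0.17)/4/0.23 = 0.1196. That shows how k was probably obtained, but not which unit the range describes.

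**2. Slack.** With c = 5, the formula needs n of about 622 for 80%. The largest tolerable design effect is 650/622 = 1.05, so the largest ICC is 0.045/64, or about 0.0007.

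**3. If k is a true between-district value.** The binomial part is multiplied by 1 + (65 − 1) × ICC:

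| EA-level ICC (assumed) | Design effect | Effective women per district | Power, t-test 8 df | Power, cluster formula |
|---|---|---|---|---|
| 0 | 1.00 | 650 | 78.8% | 80.5% |
| 0.002 | 1.13 | 576 | 77% | 79% |
| 0.005 | 1.32 | 492 | 75% | 77% |
| 0.01 | 1.64 | 396 | 72% | 73% |
| 0.02 | 2.28 | 285 | 65% | 67% |
| 0.03 | 2.92 | 223 | 60% | 61% |

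For ICCs of 0.01, 0.02 and 0.03, the reduction detectable with 80% power by the t-test is about 27%, 29% and 31%. If the between-EA coefficient of variation equals the plan's own 0.119 (ICC = 0.119² × 0.23/0.77 = 0.004), t-test power is 76%.

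**4. If 17–28% is a spread across communities.** Then k² is the sum of a district part and an EA part, k² = k_d² + k_EA². The district-level variance should use k_d² + k_EA²/10, which cannot exceed the k² in the plan. With an equal split the multiplier is 0.5 + 0.05 = 0.55, so V = 0.000492 + 0.55 × 0.001170 = 0.001136 and t-test power is about 91%. With all of k² between EAs, V = 0.000492 + 0.1 × 0.001170 = 0.000609 and power is about 99%.

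**5. If 17–28% is a range of survey estimates.** Then k already contains sampling error, and adding the full binomial term counts part of it twice. At the extreme where k holds all of it, V = 0.001170 and t-test power is about 91%.

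**The case against.** The strongest case on the other side has four parts.

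- **The direction depends on what k measures.** The 23% is introduced as the prevalence in the 2012 control clusters, and the range follows directly. On a community-level reading the EA variance is already inside k and the stated power is too low, not too high. This stands. A reader might infer that a component is missing whichever unit k describes; steps 4 and 5 show otherwise. Keeping k = 0.119 and adding an EA design effect would then double-count.
- **The size of any loss rests on an ICC the article does not give.** A reader might take 60–75% as the power the design delivers. It holds only for a true between-district k with an EA-level ICC of about 0.005 to 0.03. At 0.002 to 0.004 the t-test gives 76–77%. ICCs of 0.02 and 0.03 imply between-EA standard deviations of about 6 and 7 percentage points around 23%, wide beside the only range quoted. This also stands.
- **Mitigating features.** EA selection is stratified, which can shrink the between-EA component, and 65 women is a minimum. Both are fair, though their size cannot be judged from the article.
- **The consequences are limited.** The article reports about a 50% reduction in the earlier Botswana work; even at ICC 0.03, power for a true 35% reduction is 89%. The issue therefore bites mainly for effects near 25%, which is nevertheless the effect the trial claims to be powered for. Likewise, the gap between 78.8% and 80.5% is only approximation and not a fault in itself.

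What survives is that the section uses k as a district-level quantity, describes a two-stage sample, and allows for only one stage.

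**Conclusion.** The concern holds conditionally. The stated 80% follows from 650 independent women per district, and the plan does not sample them that way. Taking k = 0.119 as a true between-district value, the EA sampling variance is omitted and any EA-level ICC above about 0.0007 brings power under 80% by the plan's own formula. The t-test figure falls from 78.8% to between about 77% and 60% for assumed ICCs of 0.002 to 0.03, and less if stratified EA selection is effective.

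If k comes from communities or from survey estimates, the stated power may instead be conservative. The article does not settle which. An unconditional shortfall, or any single corrected power, is therefore not supported. What is supported is that the headline figure does not follow from the stated sampling design on the text's own use of k, and that the level of k must be stated before the figure can be relied on.

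**What to change.** 1. State which unit the 17–28% range and k = 0.119 describe: true district prevalences, survey estimates, or the 2012 communities.
2. Take the EA-level variance from the 2012 Botswana survey that the article already cites.
3. Recompute with both levels, counting each once:
   - With a true between-district k: V = k_d²(p0² + p1²) + [p0(1−p0) + p1(1−p1)]/650 × [1 + 64 × ICC_EA].
   - With a community-level k: split it into k_d and k_EA, and replace k² by k_d² + k_EA²/10, keeping the binomial term at 650.
   - With a k from survey estimates: remove the sampling error from k before using the first formula.
4. Restate the power for a 25% reduction, or the reduction detectable at 80%, from the 8-df t-test that will be used.

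The cost is one recalculation and possibly a less favourable stated figure. No participants are added, and the survey and primary analysis are unchanged.
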